**Fig. 2 Fig2:**
[figure not shown]
PEPMEN timeline of study procedures

### Quality control

Data collection and management are centrally monitored in all centers. The independent monitor of the study will visit each participating center at the start of inclusion, after 1 year of inclusion, and at the end of inclusion. All paravertebral procedures performed during the study will be recorded and stored for quality control. Serious adverse events related to the study procedures will be reported to the sponsor of the study without any undue delay.

### Sample size

The QoR-40 questionnaire was used as the primary outcome measure to calculate a sample size based on superiority of paravertebral analgesia when compared to epidural analgesia [21]. Backward and forward translations of the QoR-40 were validated by the study consortium to ensure the accuracy of the Dutch version. Based on previous literature, a QoR-40 score of 182 points with a standard deviation of 14 on postoperative day 3 is expected in the control group [23]. A difference of 6 points on the QoR-40 was assumed to indicate a minimally clinically relevant difference based on literature [24]. Hence, a total sample size of 172 patients is required (86 patients per group) to detect this difference with a statistical power of 80% and a significance level of (alpha) *P* < 0.05. Anticipating a 10% loss to follow up, 192 patients will be included. Only patients who withdraw before surgery will be replaced by new subjects.

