**Methods:**

This study represents a randomized controlled superiority trial. A total of 192 patients will be randomized in 4 Dutch high-volume centers for esophageal cancer surgery. Patients are eligible for inclusion if they are at least 18 years old, able to provide written informed consent and complete questionnaires in Dutch, scheduled to undergo minimally invasive esophagectomy with two-field lymphadenectomy and an intrathoracic anastomosis, and have no contra-indications to either epidural or paravertebral analgesia. The primary outcome is the quality of postoperative recovery, as measured by the Quality of Recovery-40 (QoR-40) questionnaire on the morning of postoperative day 3. Secondary outcomes include the QoR-40 questionnaire score Area Under the Curve on postoperative days 1–3, the integrated pain and systemic opioid score and patient satisfaction and pain experience according to the International Pain Outcomes (IPO) questionnaire, and cost-effectiveness. Furthermore, the groups will be compared regarding the need for additional rescue medication on postoperative days 0–3, technical failure of the pain treatment, duration of anesthesia, duration of surgery, total postoperative fluid administration day 0–3, postoperative vasopressor and inotrope use, length of urinary catheter use, length of hospital stay, postoperative complications, chronic pain at six months after surgery, and other adverse effects.

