### Outcome measures

The primary outcome measure is the total score on the Quality of Recovery 40 (QoR-40 [21]) questionnaire on the morning of postoperative day 3. The QoR-40 is a validated composite endpoint that can be used to evaluate analgesic modalities for postoperative pain control [22]. The main secondary outcome measures include the QoR-40 scores on postoperative days 1–2, the patient’s perception of postoperative pain management on days 1–3 (International Pain Outcomes (IPO) questionnaire), the need for escape pain medication on days 1–3, additional opioid consumption on days 1–3, technical complications, analgesia related side-effects, need for inotropic and vasopressive medication, length of stay on a monitored unit and in the hospital, postoperative complications, quality of life at 3 and 6 months after surgery, pain at 3 and 6 months after surgery (VAS score), and cost-effectiveness.

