### Statistical analyses

The difference in primary outcome between the two groups will be compared using an independent t-test based on the intention-to-treat principle. The primary outcome will be analyzed with a general linear model for continuous outcomes. In the analysis, the preoperative (baseline) QoR-40 measurement, age, and comorbidities will be included as potential confounders. Validity of the model (normality, homoscedasticity) will be assessed by means of residue analysis. A per-protocol analysis will additionally be performed in the same manner. Analyses of the secondary outcomes are performed depending on data type and distribution. Chi-square tests will be performed for categorical data. The t-test or Mann-Whitney U test will be used to compare continuous outcomes with a normal or non-normal distribution, respectively.

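### The primary analysis as written uses only the day-3 QoR-40, so patients without that score cannot contribute although days 1 and 2 are also measured; the risk is bias, not sample size

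*Protocol article*

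**What the plan says.** Outcome measures fixes a single time point: "The primary outcome measure is the total score on the Quality of Recovery 40 (QoR-40 [21]) questionnaire on the morning of postoperative day 3". Statistical analyses then states: "The difference in primary outcome between the two groups will be compared using an independent t-test based on the intention-to-treat principle". The same section adds a general linear model with baseline QoR-40, age and comorbidities as covariates. It does not mention the day-1 or day-2 scores, and centre, by which randomisation is stratified, is not among the covariates.

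Sample size expects "a QoR-40 score of 182 points with a standard deviation of 14 on postoperative day 3 is expected in the control group", takes 6 points as the relevant difference, requires 172 evaluable patients and continues: "Anticipating a 10% loss to follow up, 192 patients will be included". Only patients who withdraw before surgery are replaced.

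Data collection has patients complete the QoR-40 on each of postoperative days 1, 2 and 3. The article describes the secondary use of these scores in two ways. The Abstract says: "Secondary outcomes include the QoR-40 questionnaire score Area Under the Curve on postoperative days 1–3". Outcome measures says: "The main secondary outcome measures include the QoR-40 scores on postoperative days 1–2", and names no area under the curve.

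**The concern.** A t-test or an ordinary general linear model of the day-3 score needs a day-3 score. Unless values are imputed, a patient without one is left out, and the result is a complete-case comparison even though it is labelled intention-to-treat. Losses after surgery are not replaced and the form is due three days after the operation, so a missing form could well reflect a poor course. The outcome is recovery itself, and the trial's hypothesis is that side-effects and time on a monitored ward differ between the arms. Patients and staff are also unblinded. Missingness related to recovery and unequal between arms is therefore plausible, and it would distort the primary difference.

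The earlier scores are the natural information about such patients, and the named primary analysis does not use them. The secondary definition is a separate matter. An area under the curve over days 1 to 3 and separate scores on days 1 and 2 are different quantities with different numbers of tests, and the article leaves open which one is meant.

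**Working it through.** **1. The plan's own figures.** The inputs, all from Sample size, are a difference of 6, an SD of 14, alpha 0.05 and 80% power. The article does not say whether the test is one- or two-sided; a two-sided test reproduces its figure.

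- n per arm = 2 × (1.960 + 0.842)² × 14² / 6² = 85.5, rounded up to 86, so 172 in total. This reproduces. The exact t-test needs 87 per arm, a trivial difference.
- 172 / 0.9 = 191.1, rounded up to an even 192. This reproduces.
- 192 × 0.9 = 172.8, or 86.4 per arm. About 19 patients are expected to add nothing to the primary comparison.
- Power = Φ(6 / (14 × √(2/n)) − 1.96). With n = 86.4 this is Φ(2.817 − 1.96) = 80.4%. With nobody missing (n = 96) it is 84.4%.

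The sample size is right and the planned power survives the 10% loss.

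**2. Possible bias.** Let f be the proportion missing in an arm and D the number of points by which missing patients would score below those observed. The complete-case mean in that arm is too high by f × D. With the same D in both arms:

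shift in (paravertebral − epidural) = (f_paravertebral − f_epidural) × D.

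The article gives neither f by arm nor D, so these values are assumptions that average 10% missing:

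| Missing, paravertebral v epidural | D = 10 | D = 20 |
|---|---|---|
| 10% v 10% | 0 | 0 |
| 8% v 12% | −0.4 | −0.8 |
| 5% v 15% | −1.0 | −2.0 |

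Against the 6-point target, the last row is 1/6 = 17% to 2/6 = 33%. The sign reverses if the paravertebral arm loses more.

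**3. What days 1 and 2 would add in precision.** Assume that everyone missing day 3 has both earlier scores, and that the between-day correlation ρ lies between 0.3 and 0.8 (the article gives none). The large-sample variance of an arm's day-3 mean from a likelihood-based repeated-measures model is SD²/n × [1 + f/(1 − f) × (1 − R²)]. Here f = 0.10, n = 96, and R² is the share of day-3 variance explained by days 1 and 2.

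- Equal correlations, R² = 2ρ²/(1 + ρ), from 0.138 to 0.711. Effective n per arm = 96/1.0957 = 87.6 to 96/1.0321 = 93.0. Power 81.0% to 83.2%.
- First-order autoregressive, R² = ρ², from 0.09 to 0.64. Effective n per arm = 96/1.1011 = 87.2 to 96/1.04 = 92.3. Power 80.8% to 82.9%.

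Against 80.4% for complete cases, the gain is about 0.4 to 3 percentage points, and less if some of these patients also lack earlier scores.

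**4. The secondary outcome.** The Abstract's area under the curve includes day 3; the Outcome measures entry covers days 1 and 2 only. An area computed patient by patient also needs the day-3 form, so it would lose the same patients as the primary analysis.

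**The case against.** The strongest reply is that the article states no exclusion rule and that missing-data handling normally belongs in the full protocol or SAP, neither of which is shown. That stands as far as it goes: exclusion is a consequence of the named methods, and an unseen document may specify imputation. It does not remove the point, because the article does fix the primary method, and a better use of data already planned is available.

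Several stronger readings are tempting but not supported:

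- A reader might infer that the 10% sentence is itself wrong or leaves the trial underpowered. It does neither.
- A reader might take the 10% to be the sickest patients. The article gives no causes of loss.
- A reader might assume that those without a day-3 score will have scores for days 1 and 2. Nothing shows this; a critically ill patient may lack several forms.
- A reader might put the bias at up to half the target. That needs a 5% v 15% split together with a 30-point deficit (0.10 × 30 = 3.0 points), and 30 points is about 2.1 times the SD of 14. Neither figure has a source in the article.
- A reader might expect the repeated-measures model to remove the bias. It does so only if missingness depends on observed data. If it depends on the unseen day-3 value, bias remains.

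It is also fair to say that if the epidural arm loses more patients, the shift works against paravertebral analgesia and is conservative for the superiority claim. On the secondary outcome, both lists are introduced as inclusive and the area uses the same scores. The discrepancy is real but small, and it does not touch the primary analysis or the sample size.

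**Conclusion.** The point holds in a limited form. The primary analysis as written uses only day 3, cannot include patients without that score, and sets aside QoR-40 data collected on the two preceding days. The sample size and its 10% allowance are correct. What is at stake is possible bias: 1 to 2 points, 17% to 33% of the 6-point target, if missingness is 5% v 15% and missing patients score 10 to 20 points lower. Those inputs are assumptions. Equal missingness and equal deficit give no bias, and the direction depends on which arm loses more. The case for the change does not rest on power, since the gain is small. Separately, the Abstract and Outcome measures give different QoR-40 secondary outcomes and need to agree.

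**What to change.** - Keep the day-3 difference as the primary estimate, but obtain it from one repeated-measures model of the QoR-40 on days 1, 2 and 3. Include all randomised patients with at least one postoperative score.
- Model terms: arm, day, arm-by-day, baseline QoR-40, centre (the stratification factor), and the age and comorbidity terms already stated. Use an unstructured covariance over the three days.
- State that the model relies on missing at random and that patients with no postoperative score remain outside it.
- Record the reason for each missing day-3 form. Add a sensitivity analysis for patients missing through death or critical illness, for example by assigning the worst observed score, and say that this estimates a different quantity.
- Separately, name one QoR-40 secondary outcome in both the Abstract and Outcome measures: either the area under the curve over days 1 to 3 (obtainable from the same model) or the scores on days 1 and 2.

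The cost is wording in the analysis plan and one case report form field. The sample size stays at 192 and no extra questionnaire is needed. The downside is a slightly more complex primary model.

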### Statistical analyses

The difference in primary outcome between the two groups will be compared using an independent t-test based on the intention-to-treat principle. The primary outcome will be analyzed with a general linear model for continuous outcomes. In the analysis, the preoperative (baseline) QoR-40 measurement, age, and comorbidities will be included as potential confounders. Validity of the model (normality, homoscedasticity) will be assessed by means of residue analysis. A per-protocol analysis will additionally be performed in the same manner. Analyses of the secondary outcomes are performed depending on data type and distribution. Chi-square tests will be performed for categorical data. The t-test or Mann-Whitney U test will be used to compare continuous outcomes with a normal or non-normal distribution, respectively.

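### Two different analyses are stated for the single primary outcome, and the text does not say which one decides superiority

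*Protocol article*

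**What the plan says.** The Outcome measures section fixes one primary outcome: "The primary outcome measure is the total score on the Quality of Recovery 40 (QoR-40 [21]) questionnaire on the morning of postoperative day 3".

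The Statistical analyses section then gives it two analyses in consecutive sentences. The first is an unadjusted test: "The difference in primary outcome between the two groups will be compared using an independent t-test based on the intention-to-treat principle". The second, which follows directly and without any ranking against the first, is a model: "The primary outcome will be analyzed with a general linear model for continuous outcomes".

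The covariates of that model are named next: "In the analysis, the preoperative (baseline) QoR-40 measurement, age, and comorbidities will be included as potential confounders". The section closes the topic with "A per-protocol analysis will additionally be performed in the same manner", so the per-protocol analysis inherits whatever is unclear in the main one.

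Neither analysis is called primary, confirmatory, supportive or sensitivity. No other section names the deciding one.

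**The concern.** A t-test and a linear model are the same analysis only when arm is the sole term in the model. Here the model also carries prognostic covariates, so the estimate, standard error and p-value will differ from those of the t-test. With one primary outcome and two unranked tests, the text does not say what happens when one p-value falls below 0.05 and the other does not.

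Two things are at stake. First, the trial's main conclusion could rest on a choice made with both results in view. Second, a reader of the results could not check from the published plan that the reported test was the intended one. This matters more than usual because patients and care providers are not blinded (Allocation to the treatment arms), the outcome is patient-reported, and the abstract says that the results can be used to update guidelines.

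**Working it through.** **Inputs from the Sample size section.** Difference 6 points, SD 14, power 80%, alpha 0.05, 86 per group, 172 in total, 10% loss, 192 included.

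**Assumed input.** R², the share of day-3 QoR-40 variance explained by the covariates. The article gives no value, so a range of 0.05 to 0.49 is used.

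**Step 1: reproduce the plan's sample size.** For a two-sided, unadjusted comparison of two means:

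n per group = 2 × 14² × (1.960 + 0.842)² / 6² = 85.5, rounded up to 86, or 172 in total.

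172 / 0.90 = 191.1, rounded up to 192.

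Both figures reproduce. A one-sided test would need 68 per group and does not reproduce them. With 86 per group the t-test has 79.8% power (80.2% by the normal approximation). The stated size therefore fits a two-sided, unadjusted comparison.

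**Step 2: relate the two tests.** In a randomised comparison with covariates explaining R² of the outcome variance, the two test statistics are approximately bivariate normal with correlation √(1 − R²). At the planned effect the t-test statistic is centred at 6 / (14 × √(2/86)) = 2.81, and the adjusted statistic at 2.81 / √(1 − R²).

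**Step 3: results.** Adjusted power uses the noncentral t distribution with residual SD 14 × √(1 − R²) and 86 per group.

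| Assumed R² | Correlation | Type I error if either may count | Disagreement at 6 points | Power, adjusted model |
|---|---|---|---|---|
| 0.05 | 0.975 | 6.0% | 5% | 82% |
| 0.09 | 0.954 | 6.4% | 7% | 83% |
| 0.25 | 0.866 | 7.3% | 12% | 90% |
| 0.49 | 0.714 | 8.3% | 18% | 97% |

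Two independent tests would give 1 − 0.95² = 9.75%. The figures stay below that because the tests are highly correlated.

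**Step 4: check by simulation.** Trials with 86 per group and three covariates, R² from 0.1 to 0.5, 20,000 null runs per setting:

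- t-test alone: type I error 4.8% to 5.2%.
- Adjusted model alone: 4.7% to 5.0%.
- Either significant: 6.3% to 8.1%.

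At the 6-point effect, with 10,000 runs per setting, the two disagreed in 7%, 14% and 18% of trials at R² of 0.1, 0.3 and 0.5. This agrees with the approximation.

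**The case against.** **The text leans one way.** The t-test comes first, it alone carries the intention-to-treat phrase, and it is the comparison that the sample size matches. Describing the covariates as confounders fits an adjusted follow-up analysis. This is a fair inference, but it does not settle the point: the second sentence says just as plainly that the primary outcome will be analysed by the model, and the model checks that follow relate to it.

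**The full documents may settle it.** The article condenses a longer protocol, and an analysis plan may exist. Either could name the deciding test, and either could hold the coding of comorbidities, so the missing coding is not counted as a fault here. The two competing sentences are different: they are stated in the article, not omitted from it.

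**The error rate.** A reader might infer that the plan breaks its 5% level. The document does not support that. It never says that either result suffices, and each test alone holds 5%. The 6% to 8% applies only if the choice follows the data or either result may count. It also counts both directions. False claims in favour of paravertebral analgesia alone would be half of it, about 3.0% to 4.1% against 2.5%.

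**The assumed R².** Nothing in the article supports the upper end of the range. At R² of 0.05 the effects are small.

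**The choice of test.** A decisive t-test would be valid and would have the planned power. Preferring the adjusted model is a recommendation about precision, not the correction of an error.

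**Conclusion.** The point stands in a limited form. The article assigns two non-equivalent analyses to its one primary outcome and does not say which decides superiority. This is a conflict in stated text and leaves room for selection after the fact; it is not a demonstrated loss of error control.

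The size depends on the assumed R² of 0.05 to 0.49. Over that range, type I error would be about 6% to 8% if either result could count. The more practical consequence is disagreement: at the planned effect, in about 5% to 18% of trials the published text would not tell a reader whether superiority had been shown. Naming either analysis removes the problem.

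**What to change.** Before any comparison of outcomes by arm, amend the Statistical analyses text, or state in the analysis plan, that:

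1. One analysis is confirmatory. The preferred choice is the linear model already stated, for the day-3 QoR-40 total, in all randomised patients as allocated. Its terms are arm, centre, baseline QoR-40 and age. Centre is the stratification factor and is not among the listed covariates. The adjusted mean difference with its 95% confidence interval decides superiority.
2. The unadjusted t-test is a sensitivity analysis that cannot change the conclusion.
3. Any comorbidity term is specified in advance from data already recorded, or dropped.
4. The per-protocol analysis repeats the named confirmatory model.

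One check comes first. The Data collection section lists the QoR-40 only on postoperative days 1, 2 and 3, and the preoperative questionnaires it names are the EORTC instruments. The timeline figure is not available here, so a preoperative QoR-40 may exist. Confirm that it is collected before making it a term in the deciding model. Likewise, ASA class appears as an exclusion criterion but is not listed among the collected baseline data, so it should not be assumed available as a comorbidity term.

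The cost is wording and minor analysis work. The sample size stays at 172 evaluable and 192 included. Under the assumed R², the adjusted model would have about 82% to 97% power at 86 per group, against 79.8% for the t-test.

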### Time schedule

The study has started on December 3rd 2019. The first 24 months will be used for patient inclusion. After finishing patient inclusion, there will be 6 months of follow-up and an additional 6 months of data analysis.

## Discussion

Thoracic epidural analgesia has long been the gold standard for pain management following esophagectomy. However, paravertebral analgesia is increasingly suggested as a good alternative for patients undergoing MIE, as the catheter can be placed under direct thoracoscopic vision possibly reduces the incidence of hypotensive events. Furthermore, by avoiding epidural catheterization and its potentially severe neurological complications, paravertebral analgesia may be safer. However, the currently available studies mainly included patients undergoing other thoracic surgical procedures and high-quality prospective studies investigating paravertebral analgesia for esophageal cancer surgery are lacking. Therefore, the PEPMEN study aims to compare paravertebral analgesia versus epidural analgesia in patients undergoing MIE by means of a prospective multicenter randomized controlled trial.

Adequate analgesia is one of the key parts of enhanced recovery after surgery (ERAS) protocols for major surgical procedures, aiming to achieve effective pain control whilst avoiding the side-effects of high doses of systemic opioids. These aims were also described in the recently developed ERAS Society guidelines for esophagectomy, which state that regional analgesia should be the backbone of pain management in enhanced recovery after esophagectomy protocols [25]. In absence of trials in patients undergoing MIE, both epidural and paravertebral analgesia were considered to be suitable options based on extrapolated evidence, although no recommendations in favour of either modality could be made [25]. Retrospective cases series suggest that paravertebral analgesia is associated with less technical failure and reduces the incidence of hypotensive events, which may promote postoperative recovery [26, 27]. Combined with inconclusive ERAS recommendations regarding the use of either epidural or paravertebral analgesia, these retrospective findings represent an important rationale to perform a prospective randomized controlled trial comparing paravertebral and epidural analgesia regarding perioperative outcomes and treatment costs in patients undergoing MIE.

In contrast to epidural analgesia, paravertebral analgesia can only induce a unilateral sensory block of thoracic dermatomes. Nonetheless, this unilateral thoracic block is expected to achieve adequate control of chest pain after MIE, especially when combined with patient-controlled intravenous opioid analgesia as an escape for breakthrough discomfort [28]. If paravertebral analgesia in fact achieves adequate pain control, the avoidance of epidural-related side-effects likely facilitates fast recovery after MIE [29, 30], which is the primary interest of this study. Since postoperative recovery is multifactorial, a composite endpoint was considered to be most appropriate and therefore the QoR-40 questionnaire was chosen as primary outcome. The QoR-40 consists of 40 questions that are divided in separate sections that aim to evaluate the presence and extent of pain, symptoms, comfort, emotional well-being, physical independence, and satisfaction with treatment [21]. As the hypothesized advantages of paravertebral analgesia are expected to impact several of these sections, the composite QoR-40 score is considered to be a good parameter for postoperative recovery.

One might argue that the current randomized study design could be replaced by a prospective cohort study with sequential measurement of a control group followed by an intervention group which might be acceptable regarding the risk of selection bias, as the demographics of esophageal cancer patients are not expected to change within a period of a few years. However, it should be noted that the intraoperative techniques and perioperative facets of enhanced recovery protocols are continuously subjected to alterations based on new developments in the field of MIE. In case of a non-randomized sequential prospective design, changes in parts of the perioperative protocol during the study (e.g. the postoperative mobilization program) would not be possible without potentially inflicting a bias that significantly impacts the interpretability of the results. By choosing a randomized study design with stratification per center, the participating centers can still implement perioperative developments in other areas than the pain management regimen without compromising the reliability of the comparison between analgesic techniques.

In summary, the PEPMEN study is a randomized controlled multicenter trial comparing paravertebral versus epidural analgesia in patients undergoing MIE in 4 high-volume centers for esophageal cancer surgery in the Netherlands. The primary endpoint will be the quality of recovery, as measured by the QoR-40 questionnaire on postoperative day 3. By improving the quality of recovery and shortening the length of stay on the ICU, paravertebral analgesia is expected to reduce the costs of perioperative care for patients undergoing MIE. A total sample size of 192 patients is required and the duration of the study will be 3 years.

